### Power for secondary outcomes

#### Other definitions of adverse outcome

Development of Liège severe disease is estimated at 20% at 5 years.^37^ This provides approximately 41 events for the present study which is likely insufficient to develop meaningful prognostic models. Accordingly, analysis for this endpoint will be descriptive only, unless our assumptions prove incorrect and sufficient events satisfying this definition accumulate.

#### Identification of the most important MRE variables for model inclusion

Principal component analysis (PCA) will be used to reduce the number of individual MRE variables to ideally two or three eigenvector variables, for subsequent addition to the baseline clinical model. This will facilitate our ability to determine the effect on model fit of adding MRE variables.

### Retention

Participants need not undergo additional testing to enter this study. Only data obtained during routine clinical care are necessary to both define disabling disease and provide variables for model inclusion. Where participants are lost to local follow-up, participants’ general practitioner will be contacted to obtain routine clinical information, post consent (this is only applicable to METRIC cohort and those patients on retrospective cohort who have provided consent).

### Statistical methods—outcomes

#### Primary outcome

Comparative predictive ability of prognostic models incorporating MRE severity scores (MEGS, sMaRIA and Lémann index) versus models using standard characteristics alone to predict disabling CD (modified Beaugerie definition) within 5 years of new diagnosis

We will develop a multivariable prognostic model using prespecified standard predictors (age at recruitment as new diagnosis, smoking, gender, disease status at diagnosis (stricturing disease, perianal disease, severe endoscopic disease, location of disease as L1/L2/L3/L4, initial need for steroid therapy, weight loss of at least 5 kg, CRP, white cell count, faecal calprotectin, haemoglobin and platelets). Continuous variables will be retained where possible, with transformations and polynomial transformations when needed. Categorised variables will be retained as prespecified in clinical report form except where modelling requires combination of categories with small numbers. Missing covariates will be handled via multiple imputation, under the ‘missing at random’ assumption.^44^ We will compare the additive effect on model fit of each MRI score (MEGS, sMaRIA and LI as PCA variables) to the baseline standard model as a linear offset. An increase in model performance will be based on an improvement in the number of patients correctly classified for disabling disease, using models including MRE compared with a standard model. Model performance will be measured using sensitivity, specificity and net benefit. We will also assess difference in model fit using Bayesian Information Criteria (BIC) and we will report c-index for each model. Internal validation using bootstrap samples (sampling with replacement) will use at least 200 or more bootstrap samples until estimates remain stable. Model prediction at 1-year, 2-year and 3-year time horizons will also be reported.

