##### Magnetic resonance Enterography Global Score (MEGS)

This score encompasses aspects of both inflammatory activity and bowel damage, and has been validated against several reference standards, including a composite clinical reference,^30^ faecal calprotectin^31^ and capsule endoscopy^32^ (table 2).

**Table 2 T2:** Calculation of Magnetic resonance Enterography Global Score (MEGS)

Mural features	0	1	2	3	Score
Mural thickness	<3 mm	>3–5 mm	>5–7 mm	>7 mm	a
Mural T2 signal (oedema)	Normal	Minor increase	Moderate increase	Large increase	b
Perimural T2 signal	Normal	Increased signal but no fluid	Small (≤2 mm) fluid rim	Large (>2 mm fluid rim)	c
Contrast enhancement: amount	Normal	Minor increase	Moderate increase	Large increase	d
Contrast enhancement: pattern	N/A or homogeneous	Mucosal	Layered		e
Haustral loss (colon only)	None	<1/3 segment	1/3–2/3 segment	>2/3 segment	f
Mural score for that segment					a+b+c+d+e+f =g
Multiplication factor	1	1.5	2	Total segmental score g * multiplication factor	
Length of disease in that segment	<5 cm	5–15 cm	>15 cm		

Each enteric segment (jejunum; proximal ileum; terminal ileum; caecum; ascending colon; transverse colon; descending colon; sigmoid colon; rectum) is scored separately. The segmental score is then multiplied by a factor depending on the length of disease involvement in that segment. Finally, scores for extramural features are added, giving a total score (maximum possible=296). Sum all segments, then add extramural score on a per-scan basis; five points for each of^1^: lymph nodes >1 cm short axis,^2^ comb sign (linear structures on the mesenteric border of an affected bowel segment),^3^ abscess and fistula^4^.

N/A, not applicable.

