##### Lémann Index (LI)

The LI^34^ (table 4) is based on comprehensive assessment of structural bowel damage, including stricturing, penetrating lesions (ﬁstulae and abscesses) and surgical resection, and is applicable to different settings, such as early or advanced disease, patients with or without surgery, or with different CD locations and extension. The score comprises several factors that can be assessed either clinically, or using imaging or via endoscopy. We will use the imaging-derived score. Since the anal canal will not have been imaged specifically for METRIC, we will omit this score.

**Table 4 T4:** Derivation of the Lémann Index

Organ	Method of assessment	N*	Segment	Grade 1	Grade 2	Grade 3
Surgical interventions†						
Upper tract	History	3	Oesophagus, stomach, duodenum	–	Bypass diversion or stricturoplasty	Resection
Small bowel	History	20	Each 20 cm SB segment	–	Bypass diversion or stricturoplasty	Resection
Colon/rectum	History	6	Each colonic segment	–	Stoma, bypass diversion or stricturoplasty	Resection
Stricturing lesions						
Upper tract	MRI	2	Stomach, duodenum	Wall <3 mm; segmental enhancement without prestenotic dilatation	Wall thickening ≥3 mm or mural stratification with no prestenotic dilatation	Stricture with prestenotic dilatation
Small bowel	MRI	20	Each 20 cm SB segment	Wall <3 mm; segmental enhancement without prestenotic dilatation	Wall thickening ≥3 mm or mural stratification with no prestenotic dilatation	Stricture with prestenotic dilatation
Colon/rectum	MRI	6	Each colonic segment	Wall <3 mm; segmental enhancement without prestenotic dilatation	Wall thickening ≥3 mm or mural stratification with no prestenotic dilatation	Stricture with prestenotic dilatation or >50% of the lumen
Penetrating lesions						
Upper tract	MRI	2	Stomach, duodenum	–	Deep transmural ulceration	Phlegmon or fistula
Small bowel	MRI	20	Each 20 cm SB segment	–	Deep transmural ulceration	Phlegmon or fistula
Colon/rectum	MRI	6	Each colonic segment	–	Transmural ulceration	Phlegmon or fistula

*n is the number of segments within a particular organ.

†This information will be collated from the original METRIC records, although a relevant surgical history will be very rare since included patients are, by definition, those with a new diagnosis of Crohn’s disease.

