#### Alternative definitions of disabling disease

Since the Beaugerie criteria are imperfect, further definitions of adverse outcomes will also be collected; specifically the Liège criteria^37^ and Montreal behaviour criteria.^39^

The Liège criteria are met if any of the following occur:

Development of complex perianal disease.Any colonic resection.Two or more SB resections.A single SB resection of >50 cm.Definitive stoma.

Complex perianal disease is defined as per the American Gastroenterological Association,^40^ and the perianal disease modifier will be collected.

The Montreal behaviour criteria classify CD as either inflammatory (B1), stricturing (B2) or penetrating (B3). Stricturing disease will be defined as a fixed luminal narrowing of >50% relative to normal proximal bowel. Penetrating disease will be defined as an intra-abdominal or enterocutaneous fistula, inflammatory mass, or abscess.

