We believe this is the first study to investigate MRI as a predictive biomarker for development of disabling disease in newly diagnosed CD. In a dual-centre prospective study of 142 CD patients, Fiorino *et al* evaluated the predictive role of MRE on disease outcome and found that bowel damage on imaging was associated with increased future hospitalisation and surgery.^27^ However, patients were eligible if imaging was acquired within 2 years of a potential diagnosis of CD, so was not representative of a newly diagnosed cohort. A single-centre study enrolled 112 patients with relapsed CD (rather than new diagnoses) and conducted both MRE and colonoscopy.^26^ Future surgical resection was related to the presence and degree of established bowel damage (stricture, fistula or abscess) rather than the degree of inflammation. Most recently, a single-centre study of 52 patients with CD (not stratified by new diagnosis/suspected relapse) found that the presence of restricted diffusion, increased upstream dilatation from a stricture, complex fistula, perienteric inflammation, fibrofatty proliferation and increased length of disease involvement on outpatient MRE were significantly more common in patients progressing to surgery.^45^ It is unknown if these findings can be extrapolated to new diagnoses, who, by definition, are earlier in their disease trajectory than those with relapsed, established CD.^26^ Nevertheless, these studies suggest that the degree of established bowel damage may predict future adverse outcomes, rather than the degree of inflammation encountered during a flare. Unlike other biomarkers such as CRP and calprotectin, MRE has the advantage of being able to quantify both bowl damage and inflammation simultaneously.

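### The standard model has a stricturing term but no penetrating term, which can give MEGS and the Lémann Index credit for disease already known clinically

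*Protocol article*

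**What the plan says.** In the Protocol article, Statistical methods—outcomes, Primary outcome, the comparator is fixed in advance: "We will develop a multivariable prognostic model using prespecified standard predictors". Besides age, smoking and gender, the list has "disease status at diagnosis (stricturing disease, perianal disease, severe endoscopic disease, location of disease as L1/L2/L3/L4", followed by "initial need for steroid therapy, weight loss of at least 5 kg, CRP, white cell count, faecal calprotectin, haemoglobin and platelets". No penetrating, fistula or abscess term appears, and no other section adds one or explains its absence.

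Under Alternative definitions of disabling disease, the protocol states: "The Montreal behaviour criteria classify CD as either inflammatory (B1), stricturing (B2) or penetrating (B3". It defines the third class separately: "Penetrating disease will be defined as an intra-abdominal or enterocutaneous fistula, inflammatory mass, or abscess". The Secondary outcomes section groups B2 and B3 together as the adverse phenotype.

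Two of the three MRE scores contain the missing feature. The footnote to the MEGS table adds five points for each listed extramural item, ending with "abscess and fistula". The Lémann Index "is based on comprehensive assessment of structural bowel damage, including stricturing, penetrating lesions", and its table puts phlegmon or fistula at grade 3. The sMaRIA table has only wall thickness, oedema, fat stranding and ulceration.

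**The concern.** The primary outcome is the gain from MRE over standard characteristics. That gain is interpretable only if the comparator holds what a clinician would already know about behaviour at diagnosis. Here it holds one half of complicated behaviour (stricturing) and leaves out the other (penetrating).

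If penetrating disease is prognostic and is known from surgery, CT, endoscopy or clinical findings, a score that rises in those patients will look useful even if it carries nothing further. The error runs in one direction, in favour of MEGS and the Lémann Index.

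Secondary outcome 1 reuses the same modelling to predict B2/B3. There the standard model identifies patients who are already stricturing at diagnosis but not those who are already penetrating, while two of the MRE scores can see both.

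**Working it through.** **1. The plan's own figures.** From Assumptions: 207 participants, prevalence of disabling disease 55–60%. Events: 207 × 0.55 = 113.9 and 207 × 0.60 = 124.2. Non-events: 207 × 0.45 = 93.2 and 207 × 0.40 = 82.8. These reproduce the stated 114–124 and 83–93.

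**2. Who carries which feature.**

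| Feature at diagnosis | Standard model | MEGS | Lémann Index | sMaRIA |
|---|---|---|---|---|
| Stricturing | own term | no separate item | graded | no item |
| Internal fistula, abscess or phlegmon | none | abscess 5, fistula 5, of a maximum 296 | phlegmon or fistula, grade 3 | no item |
| Perianal | own term | no item | anal canal omitted | no item |

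One MEGS item is 5/296 = 1.7% of the maximum, so the Lémann Index is the more exposed of the two.

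**3. Mechanism.** Take a score that equals noise (SD 1) plus a shift in penetrating patients and carries no other information. Add it to a logistic standard model (c-index about 0.70, event rate about 56%) without and then with a penetrating term. The documents give neither the prevalence of penetrating disease at diagnosis nor its effect, so these are assumptions: prevalence 5–15%, odds ratio 2–4, shift 0–2 SD. Each scenario used 400,000 simulated patients, with the likelihood-ratio (LR) gain scaled to 207.

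- Without the term, the c-index gain is 0.000 to 0.011 and the expected LR gain is 0.0 to 2.9.
- With the term, both gains fall to zero in every scenario.

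**4. What that means in one study.** BIC prefers the larger model when the LR statistic exceeds ln(207) = 5.33. Treating the expected gain λ as the noncentrality of a chi-square on 1 df, the chance of a false preference is P(χ²₁(λ) > 5.33). With λ = 0 it is 2%.

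| Prevalence | Odds ratio, shift | λ | False BIC preference |
|---|---|---|---|
| 5% | 4, 1 SD | 0.13 | 3% |
| 5% | 4, 2 SD | 0.50 | 6% |
| 10% | 4, 1 SD | 0.46 | 5% |
| 10% | 4, 2 SD | 1.61 | 15% |
| 15% | 2, 1 SD | 0.29 | 4% |
| 15% | 4, 1 SD | 0.93 | 9% |
| 15% | 4, 2 SD | 2.92 | 27% |

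Simulating whole studies of 207 agrees. The false-preference rate was about 2–6% at 5% prevalence and 18–24% in an extreme corner (15%, odds ratio 5, shift 1.5 SD), against 2–4% with the term included.

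**5. The lead criterion.** The protocol judges improvement first by the number of patients correctly classified. At a 0.5 threshold, prevalence 5–15%, and either odds ratio 3 with a 1.0 SD shift or odds ratio 5 with a 1.5 SD shift, the undue gain is 0.1 to 1.4 patients of 207 and 0.000 to 0.007 in net benefit.

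**6. Cost of adding a term.** The list has 14 predictors, or 16 parameters if location takes 3 df and the rest 1 each. Non-events per parameter are 83/16 = 5.2 to 93/16 = 5.8. With 17 parameters they are 83/17 = 4.9 to 93/17 = 5.5.

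**The case against.** The strongest reply is that internal fistula or abscess at diagnosis may be found mainly by MRE. Every participant has an MRE around diagnosis, and crediting MRE for what it finds is the purpose of the study. That is correct for lesions seen only on MRE. The bias concerns lesions known from other sources, and the documents do not say how many there are. The reply does not explain why stricturing disease, also often an imaging finding, is in the list.

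A second reply is that CRP, white cell count, calprotectin, haemoglobin, platelets, weight loss, steroid need and severe endoscopic disease absorb part of the signal. This stands too. The simulation lets penetrating disease be independent of the other predictors, so it leans towards overstating the effect.

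Third, the supporting evidence in the Discussion, which relates later resection to "established bowel damage (stricture, fistula or abscess) rather than the degree of inflammation", comes from relapsed patients with surgery as the outcome. The protocol itself says that it is unknown whether this extends to new diagnoses. It makes an effect plausible but does not establish one for the modified Beaugerie outcome.

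A reader might infer that penetrating patients are lumped with mild disease, that all the MRE scores gain, and that the primary comparison is therefore seriously biased. The documents do not support this. The coding overlap is on the behaviour term only, sMaRIA has no penetrating item, and the size of the effect rests wholly on assumptions.

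**Conclusion.** The point holds as an inconsistency in the prespecified predictor list with a known direction and a probably small size. The comparator recognises B2 but not B3, although the protocol treats B2 and B3 together as complicated disease. The omission can favour MEGS and, more so, the Lémann Index.

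Under the assumed ranges the effect is negligible at about 5% prevalence and becomes material at about 10–15% only with a strong prognostic effect and a clear shift in the score. BIC is more sensitive to it than correct classification is, where the gain is about one patient. The primary comparison is not invalidated.

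The case is stronger for secondary outcome 1, because baseline penetrating disease is itself part of the outcome category and the standard model cannot identify it.

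**What to change.** In the Primary outcome paragraph of Statistical methods, prespecify a comparison in which the stricturing term is replaced by Montreal behaviour at diagnosis. Make it the standard model or at least a sensitivity comparison, and apply it to secondary outcome 1 as well. There are two workable codings:

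- **B2 or B3 versus B1, one indicator.** This adds no parameter and matches the protocol's own grouping, but the separate stricturing term is lost.
- **B1, B2, B3.** This keeps the distinction and adds one parameter, taking non-events per parameter from 5.2–5.8 to 4.9–5.5.

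Where records allow, take baseline behaviour from sources other than the study MRE. Putting MRE-derived behaviour in the comparator would bias against MRE. The article does not show that sites record the source of baseline behaviour, so where it cannot be separated, report the comparison both ways. The change needs a few lines of plan text and, for the source of the finding, some extra baseline abstraction at sites.

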#### MRE activity scores

We will calculate established MRE activity indices as follows.

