### Outcomes

#### Primary outcome

Comparative predictive ability of prognostic models incorporating MRE severity scores (MEGS, sMaRIA and Lémann index) versus models using standard characteristics alone to predict disabling CD (modified Beaugerie definition) within 5 years of new diagnosis.

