#### Adequacy of this number of events/non-events

Calculating sample sizes for prognostic studies suffers from a relative lack of readily applied methods suitable for all study designs, since sample size for development depends on whether the primary aim is to select potential variables for a new model (via univariable significance within a data set), or to evaluate a model where the variables have been prespecified and are therefore fixed. In the present study, the variables are fixed since we are explicit that we will test a small number of MRE scores in the context of a model using fixed clinical (?clinicopathological) variables. Therefore, recommendations for sample sizes relevant to external validation are most appropriate. Accordingly, the literature suggests we require 80–100 events for model evaluation where variables are prespecified and fixed.^41^ This also provides sufficient power to assess whether addition of the three MRE scores enhance prediction, under the widely used ‘rule-of-thumb’ of 10–20 events per variable.^42^ We note that recent methods to calculation external validation sample size did not exist in 2017, when this study was powered.^43^

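### As worded, the primary analysis enters the MRE scores as PCA variables, so it does not deliver the score-by-score comparison that the primary outcome names

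*Protocol article*

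**What the plan says.** **The question.** In the protocol article, Outcomes, Primary outcome, the comparison is of "prognostic models incorporating MRE severity scores (MEGS, sMaRIA and Lémann index) versus models using standard characteristics alone". The section MRE activity scores opens with "We will calculate established MRE activity indices as follows". It then sets out rules for each index: MEGS has length multipliers of 1, 1.5 and 2 and 5-point extramural items; sMaRIA gives 2 points for ulceration and 1 for each other feature; LI grades damage by segment.

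**The sample-size reasoning.** Under Adequacy of this number of events/non-events, the article argues that "the variables are fixed since we are explicit that we will test a small number of MRE scores". On that footing it states that "the literature suggests we require 80–100 events for model evaluation where variables are prespecified and fixed".

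**The analysis.** Under Statistical methods—outcomes, Primary outcome, the plan compares the additive effect on model fit of "each MRI score (MEGS, sMaRIA and LI as PCA variables) to the baseline standard model".

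**PCA elsewhere.** Under Power for secondary outcomes, PCA is to "reduce the number of individual MRE variables to ideally two or three eigenvector variables". Secondary outcome 2 likewise applies it to individual MRE parameters. Secondary outcome 1 takes its modelling from the primary outcome.

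**The concern.** A principal component is a weighted sum whose weights come from the correlations in the sample at hand. MEGS, sMaRIA and LI are also weighted sums or graded scores, but their rules were set beforehand. If a component takes the place of an index, the predictor tested is no longer that index, and a result for the component says nothing definite about whether MEGS, sMaRIA or LI adds to the standard predictors.

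That per-score answer is what the primary outcome promises and what a radiologist could use. The secondary objectives also foresee external evaluation of the MRE-based model. A model built on components would have to carry this sample's loadings with it, whereas the indices can be scored from a scan by established rules. The same wording would govern the Montreal and Liège models, if these are developed.

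**Working it through.** **1. The plan's own figures.** Inputs: N = 207 and a prevalence of 55%–60% (Assumptions; Sample size and justification).

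- Events: 207 × 0.55 = 113.85 and 207 × 0.60 = 124.2, i.e. 114–124.
- Non-events: 207 × 0.40 = 82.8 and 207 × 0.45 = 93.15, i.e. 83–93.

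Both ranges reproduce. Three MRE terms give 83/3 = 27.7 to 93/3 = 31.0 non-events per added MRE term, whether the terms are three scores or three components. Two components would give 83/2 = 41.5 to 93/2 = 46.5. The PCA wording changes none of the stated counts.

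**2. What the phrase can mean.** PCA of one total returns that total, rescaled. The phrase therefore has content in three cases:

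- *Across the three totals.* Each component mixes MEGS, sMaRIA and LI, so the gain from one component belongs to no single score.
- *On the items within a score.* The established weights are replaced by loadings estimated from this sample.
- *For LI alone.* MEGS and sMaRIA are tested as named, but LI is not.

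In each case at least one index is not tested as described under MRE activity scores.

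**3. Retaining all components.** If all three components of the three totals enter together, they are a rotation of the standardised scores, and the likelihood and BIC are those of the three scores entered together. Coefficients can be rotated back, but each then describes a score adjusted for the other two. It is not the gain from adding that score alone to the baseline model.

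**4. Illustration.** The article gives no correlations between scores, so these are assumed: r between scores 1 and 2, and 0.8r between each of them and score 3, with r = 0.4, 0.6 and 0.8. One logistic data set of 207 patients was simulated per value, with five baseline covariates and an outcome that depends on score 3. BIC (lower is better):

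| r | Baseline | Three scores | Three components | First component | Score 1 / 2 / 3 alone |
|---|---|---|---|---|---|
| 0.4 | 281.10 | 281.585 | 281.585 | 272.97 | 278.90 / 282.75 / 275.97 |
| 0.6 | 297.40 | 306.91 | 306.91 | 298.83 | 300.90 / 301.44 / 296.31 |
| 0.8 | 261.76 | 268.946 | 268.946 | 263.80 | 266.18 / 265.68 / 259.21 |

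The two joint fits are identical, as step 3 requires. At r = 0.6 and 0.8 the first component does not improve on baseline while score 3 alone does. At r = 0.4 the first component beats every single score. The two specifications can disagree in either direction. These are single simulated data sets and do not estimate what this study will find.

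Bootstrap standard deviations of the first component's loadings were 0.006–0.034, so instability of the loadings was small in this setting. The issue is what is being tested.

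**The case against.** The strongest reply is that the parenthesis is ambiguous. The same sentence promises the effect of each score, the heading above it repeats the primary outcome, and secondary outcome 1 names the three scores without PCA. The phrase may attach to LI alone or have been carried over from secondary outcome 2. A condensed article may also leave PCA inputs and scaling to a fuller document. This stands as a limit on the point: a reader might infer that the study cannot evaluate the established indices at all, and the article does not establish that. It does not remove the conflict, because the article states a rule for the primary analysis, and every reading that gives the rule content departs from the named scores.

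A reader might also infer that the fixed-variables premise collapses and the sample size with it. The article does not support this. It contrasts fixed variables with selection by univariable significance, and PCA does not look at the outcome. The candidate scores remain named in advance; only the loadings, and the number of components if chosen from the data, are not.

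Nor can the two-or-three range be multiplied by three scores to claim many extra terms. It refers to the pooled individual MRE variables under a secondary outcome.

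Finally, any model developed here needs its estimated coefficients published, and loadings could be published with them. That is fair and weakens the external-evaluation argument, but a published component is still not MEGS, sMaRIA or LI.

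**Conclusion.** The point holds in a limited form. The PCA wording in the primary analysis conflicts with a primary outcome framed on named severity scores and fits poorly with the claim that the MRE variables are fixed. Followed as written, the added value of one or more indices could not be attributed to that index, and secondary outcome 1 would inherit this.

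The conclusion rests on comparing the sections and on what PCA does algebraically. It does not depend on the assumed correlations, which only illustrate that conclusions based on BIC can differ. The joint contribution of all three totals would remain testable if every component were kept. The wording should be corrected before analysis, but it does not undermine the study's size or data.

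**What to change.** In Statistical methods—outcomes, Primary outcome, delete the words that make the scores PCA variables. State that each index enters directly as its prespecified patient-level score, one score per model, against the same baseline model.

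Fix the patient-level form of each score before analysis. The article defines a total for MEGS, but gives sMaRIA per segment and LI as segment grades with the anal canal omitted. The aggregation of these two should be written down, or cross-referenced if a fuller document already has it.

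Confine PCA to secondary outcome 2 and repeat it inside each bootstrap sample there, so that internal validation covers the estimation of the loadings.

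If PCA is truly intended for the primary analysis, state its inputs, scaling and number of components in advance, and reword the primary outcome and the fixed-variables argument to match.

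The cost is a wording change and, on the first option, a simpler analysis. No new data or participants are needed and no stated event count changes.

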### Assumptions

We assume the prevalence of our modified Beaugerie definition of disabling disease will be approximately 55%–60%; this is informed primarily by the external validation cohort^37^ of the Beaugerie descriptors, in which 57% of 361 participants had developed disabling disease by 5 years. In support, a local audit of 33 newly diagnosed patients at one METRIC recruitment centre found 5 of 33 (15%) patients met the definition by mean 11.3 months, giving 16% at 1 year. Extrapolation to 5 years gives 58% prevalence, similar to that expected from the literature.^37^ We assume that development of disabling disease is approximately linear over time. Therefore, 207 participants will provide 114–124 events and 83–93 non-events (defined by non progression to disabling disease); the smaller proportion defines the minimum sample size for powering a modelling study, where regression methods are used for development (see section below).

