### Sample size and justification

The sample size was based on including 207 participants newly diagnosed with CD. During the study, due to problems obtaining consent for additional follow-up hampered by COVID-19, the original target recruitment was necessarily reduced from 167 to 131 from the METRIC prospective cohort, and so an increased target of 76 participant retrospective cohort recruited from METRIC sites is anticipated. We anticipate this sample size will provide between 114 and 124 events (83–93 non-events). The number of the retrospective cohort will be increased to meet the 207 participant target if recruitment to the METRC cohort is below 131.

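### Holding a standard model developed in the same patients as an offset shrinks the MRE coefficient and understates the BIC gain from the MRE scores

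*Protocol article*

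**What the plan says.** Under Statistical methods—outcomes, Primary outcome, the Protocol article states: "We will develop a multivariable prognostic model using prespecified standard predictors". It lists fourteen predictors, among them stricturing, disease location, endoscopic severity, CRP and faecal calprotectin. It continues: "We will compare the additive effect on model fit of each MRI score (MEGS, sMaRIA and LI as PCA variables"), and these are added "to the baseline standard model as a linear offset".

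Only one study population is described: "The sample size was based on including 207 participants newly diagnosed with CD". Validation is internal, by bootstrap. The article names no published coefficients for the standard model, no shrinkage of the offset and no joint refit.

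The main criterion for improvement is the number of patients correctly classified, measured by sensitivity, specificity and net benefit. BIC is an additional measure of fit, and the c-index is reported. Secondary outcome 1 is modelled in the same way. Secondary outcome 2 judges the significance of MRE features by the improvement in BIC.

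The primary outcome itself is worded in terms of the scores: "Comparative predictive ability of prognostic models incorporating MRE severity scores (MEGS, sMaRIA and Lémann index) versus models using standard characteristics alone".

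**The concern.** An offset holds the standard linear predictor at coefficient 1 while the MRE term is estimated. That is sound when the standard model was fixed in other data. Here it is estimated in the same patients without MRE in the model, so any standard predictor correlated with the score has already been credited with part of the score's effect. Only the remainder is left for MRE.

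Correlation is likely on the article's own content. MEGS is described as validated against faecal calprotectin, a standard predictor. Table 4 grades the Lémann Index partly on strictures (grade 3 is "Stricture with prestenotic dilatation"), and stricturing disease at diagnosis is also a standard predictor.

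At stake are the BIC comparison, which also serves as the significance criterion in secondary outcome 2, and the MRE coefficient that will be reported.

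**Working it through.** **1. The plan's own figure.** The Assumptions section says "207 participants will provide 114–124 events and 83–93 non-events", from a prevalence of 55–60%. Events: 207 × 0.55 = 113.9 and 207 × 0.60 = 124.2. Non-events: 207 × 0.45 = 93.2 and 207 × 0.40 = 82.8. The figures reproduce.

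**2. Size of the standard model.** Thirteen of the fourteen predictors at one degree of freedom each, plus three for the four location categories, gives 16. This assumes binary smoking and linear continuous terms.

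**3. Algebra (linear model).** Let x be the centred MRE score, y the outcome, and M the projection that removes the standard predictors.

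- Joint fit: b = x′My / x′Mx
- Offset fit: b = x′My / x′x
- Ratio, offset to joint: x′Mx / x′x = 1 − R2

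The z-value shrinks by √(1 − R2). For logistic regression this is only a guide. With a joint coefficient of 0.55 it predicts 0.55 × 0.7 = 0.39 at R2 = 0.3 and 0.55 × 0.5 = 0.28 at R2 = 0.5.

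**4. Logistic simulation.** From the article: n = 207 and a prevalence within 55–60% (57.5% in the runs at log-odds 0.4). Assumed: the true MRE log-odds per SD, R2, the strength of the standard model and how the correlation is spread over the predictors. BIC favours the score when twice the log-likelihood gain exceeds ln(207) = 5.33. The MRE term costs one degree of freedom under either method.

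| True log-odds per SD | R2 | Coefficient, joint | Coefficient, offset | BIC favours score, joint | BIC favours score, offset |
|---|---|---|---|---|---|
| 0.4 | 0 | 0.45 | 0.41 | 62% | 58% |
| 0.4 | 0.2 | 0.45 | 0.37 | 48% | 39% |
| 0.4 | 0.4 | 0.45 | 0.31 | 38% | 21% |
| 0.4 | 0.6 | 0.45 | 0.23 | 24% | 6% |
| 0.5 | 0.3 | 0.55–0.56 | 0.36–0.41 | 65% | 44–50% |
| 0.5 | 0.5 | 0.55–0.56 | 0.26–0.32 | 48–52% | 15–22% |

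Ranges span separate simulation set-ups at the same true effect and R2. At log-odds 0.4 and R2 = 0.4, letting the score correlate with only 4 of the 16 predictors gave a larger loss: coefficient 0.27 against 0.44, and BIC 16% against 35%.

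The bias is not a small-sample effect. At n = 5,000, R2 = 0.4 and a true value of 0.50, the offset fit gives 0.38 and the joint fit 0.50.

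**5. The stated main criterion.** Performance in new patients:

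- Log-odds 0.4, R2 = 0.4: gain in correct classification of 0.7 percentage points with the joint fit and 0.9 with the offset. The apparent gain, in the development data, was 0.9 against 0.6.
- Log-odds 0.5, R2 = 0.3, first set-up: c-index 0.725 joint and 0.726 offset; correct classification 66.9% for both; net benefit at threshold 0.5 of 0.234 and 0.235.
- Log-odds 0.5, R2 = 0.3, second set-up: c-index 0.709 joint and 0.704 offset; correct classification 65.6% and 65.3%.

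**6. Scores or components.** The Primary outcome under Outcomes names the three scores, and the section on adequacy of events speaks of adding three MRE scores. The sections on identifying important MRE variables and on secondary outcome 2 apply PCA to individual MRE features. Only the offset sentence describes the three scores as PCA variables. As written, it is unclear whether scores or components enter the primary analysis.

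**The case against.** The strongest reply is that the main criterion is barely touched. Improvement is to be judged by correct classification, sensitivity, specificity and net benefit, with BIC alongside. In new patients the offset and joint models performed about equally: the shrunken MRE coefficient is paired with standard coefficients that carry the shared signal. This stands, and it limits the point to model fit and the coefficient. Only the apparent, uncorrected gain in classification fell, and the planned bootstrap addresses apparent performance.

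A second reply is that the wording is loose and the article is condensed. The offset could be fixed externally, in which case the argument would not apply. It could be shrunk for optimism first: with a true value of 0.40 this brought the coefficient to 0.44 at R2 = 0.2 and 0.4, removing most of the attenuation. But neither step is stated. The section on adequacy of events calls the variables fixed, not their coefficients. The offset is a stated rule, not a detail left open.

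A third reply is that R2 is unknown. That is correct, so the size can only be given as a range.

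**Conclusion.** The point holds for model fit and the reported coefficient. With an offset estimated in the same patients, the MRE coefficient is attenuated and the BIC improvement understated to the extent that the score correlates with the standard predictors. At a true log-odds of 0.5 per SD, the chance that BIC favours the score drops by 15 to 21 percentage points at R2 = 0.3 (65% to 50% or 44%), and from about 50% to 15–22% at R2 = 0.5. At R2 = 0 the loss is small (62% to 58% at log-odds 0.4). The effect sizes and R2 values are assumptions; the direction is not.

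A reader might infer more than the documents support:

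- That the whole primary comparison is tilted against MRE, making a false negative on the study question likely. The main criterion is classification, where the out-of-sample loss was nil to small.
- That a significance test loses power or has the wrong size. The primary outcome section plans no likelihood-ratio test.
- That the Lémann Index suffers most. The overlap with stricturing makes this plausible, but there is no figure behind it.
- That the offset model would predict badly in use. The simulations do not show this.

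**What to change.** For the model-fit comparison and the reported coefficients, replace the offset by a joint fit: refit the standard predictors together with each MRE score and compare the nested models by BIC. Keep an offset only if its coefficients are fixed externally, and then name the source. Apply the same rule to secondary outcomes 1 and 2.

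In the same sentence, state that MEGS, sMaRIA and the Lémann Index are entered as scores in the primary analysis, and keep PCA for secondary outcome 2.

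The cost is a sentence or two, with no new data or patients and no extra degrees of freedom for the MRE term. There is a small downside: at this sample size the joint fit slightly overestimates the MRE coefficient (about 0.55 for a true 0.5), which the planned bootstrap can quantify.
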